### Intervention content

Figure 3 shows a thematic representation of the program goals with the targets and the strategies adopted at individual and group level using the behaviour techniques. The intervention will focus primarily on key behavioural risk factors, including unhealthy diet, physical inactivity, tobacco use, alcohol use, and sleep. Based on the dietary recommendations for the prevention of T2DM
^
39
^ and pertinent research findings among individuals with IFG, the dietary intervention will include consumption of a low-calorie diet (~1500 calories per day i.e., 500 calories lower than the daily requirement for women)
^
39,
42–
44 
^and consuming food with low glycaemic index. Other dietary recommendations include changing the quality of dietary fat from using saturated to unsaturated, increasing the intake of whole grains and foods rich in fibre and decreasing the intake of sugar-sweetened beverages, sweets, and highly processed products
^
45–
47
^. The dietary goals are: <30% of total energy intake from fat, 400–600 grams of fruit and vegetable intake a day, 5 cups (400 gms of cooked rice intake per day), <25 gms of free sugar intake a day, and <5 gms of salt intake per day
^
45
^. The adherence to diet will be assessed every month using a 24-hour dietary recall
^
48
^. Other measures of intervention goal include increasing physical activity to the recommended levels of at least 150 minutes of moderate-vigorous physical activity per week
^
40
^. 7–9 hours of sleep at night
^
41,
49
^, and no use of alcohol and tobacco.

**Figure 3. f3:**
[figure not shown]
Thematic representation of the program goals, targets and individual-group tailored strategies using behaviour change techniques

### Intervention delivery

The intervention will be delivered through 12 sessions (individual and group based), one session per month, over a period of 1 year (
Table 3). Intervention delivery will be supported using pretested and piloted educational materials such as flip charts for group-based sessions and a mobile based application for individual sessions. The mobile application will also serve as an interactive platform for a personalized diet planning and reporting.

The group sessions (45–60 minutes duration) will be organised in the participants’ neighbourhood, mostly in homes or local health centres, delivered by the research team (postgraduates in public health/ social work degree) in the initial phase, followed by trained volunteers as “peer mentors”. Peer mentor, a group nominated volunteer, will undergo a five-day capacity building training program to guide and assist the participants in making realistic goals for lifestyle modification with the support of the extended community stakeholders.

### Evaluation framework

In addition to the baseline, 12th month and 24
^th^ month assessment for the primary and secondary outcomes, process evaluation of core interventions at community, peer mentor and participant levels will be undertaken (
Figure 4). Evaluation process will be facilitated through regular monitoring via participant feedback report, peer mentor feedback report, feedback on quality of training, pre- and post-training knowledge evaluation and other interactions (mobile app/telephonic contact). 

**Figure 4. f4:**
[figure not shown]
Theory of change Framework.

### Data analysis

Data will be collected and entered using a data entry template in an ODK platform by the data collectors and managed in a cloud-based server which will only be accessed by the Principal Investigator (EM). Subsequent to the data collection, the data will be used only using a participant identity number and all the personal identifiers will be masked. Only deidentified data will be shared with other investigators, if required. Data quality will be ensured during data collection and data analysis. During the data collection, the research team will verify the data for missing values and if present, will be rectified then and there. Furthermore, randomly identified 5% of the participants data will be verified with the participants through telephone for quality check. The data from the ODK platform will be exported to SPSS and data cleaning will be done manually. Any outliers or implausible values will be identified and will be checked with participants over phone, if necessary.

The analysis will follow the intention-to-treat (ITT) principle. Characteristics of the participants at baseline will be compared between study groups using descriptive statistics. The primary outcome will be analysed using the generalized estimating equations (GEE) with an appropriate working correlation structure and a binomial family with 'log' link function to estimate the relative risk (and 95% confidence interval [CI], p value). Standard errors will be based on Huber-White sandwich estimator, which will provide valid CIs even in case of misspecification of the correlation structure
^
50
^. For secondary outcomes, continuous variables will be analysed using mixed-effects linear regression models, which will include all available data at baseline, 12 and 24 months. Study group (intervention vs. control), timepoint (follow-up vs. baseline) and a study group-by-time point interaction will be specified as fixed effects. Random effects will be specified for wards, to account for the clustered study design, and for participants, to account for correlation between the repeated measurements on the same individual. Categorical variables will be analyzed using log-binomial models. All p values reported will be 2 tailed, and a p of 0.05 will be considered statistically significant. Analyses will be performed with
Stata version 14.2 (StataCorp LP, College Station, Texas, USA). 

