### Study participants

**
*Inclusion criteria*:** 1) Women aged 30–60 years; 2) overweight or obese (waist circumference ≥80 cm)
^
22
^; 3) no prior history of diabetes; 4) not taking any glucose-lowering medications; 5) no prior history of gestational diabetes mellitus (GDM); 6) able to read, write and speak Malayalam, the local language; 7) consents to participate in the trial; and 8) diagnosed with i-IFG (fasting plasma glucose [FPG] 5.6-6.9 mmol/l and 2-hr plasma glucose [2-hr PG] <7.8 mmol/l) on a 2-hr oral glucose tolerance test (OGTT)
^
3
^.

**
*Exclusion criteria*:** 1) Women with known T2DM; 2) having GDM; 3) prior history of GDM; 4) breastfeeding women; 5) having major chronic illnesses including mental disorders, that are likely to impede consenting and participation in the intervention program; 6) taking medications that could alter glucose metabolism (e.g., corticosteroids); and 7) diagnosed with normoglycemia, IGT, and T2DM, as per the American Diabetes Association criteria
^
3
^ on the OGTT.

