### Sample size and randomization

We assumed that the cumulative incidence of regression to normoglycemia at two years would be 18% in the control group (based on unpublished data from the K-DPP trial) and that there would be a 50% relative risk in conversion to normoglycemia with the intervention. The sample size required in each study group was 475 with a type 1 error of 5%, at least 80% power, a contamination rate of 15%, and a 10% loss to follow-up. The sample size required with same estimates and 90% power in each group is 625, and will be recruited, if logistically feasible.

The estimated sample size of 950 participants will be randomly allocated in a 1:1 ratio to the control group and the intervention group using a computer-generated randomization sequence using Microsoft excel by an independent statistician not involved in the trial. The independent statistician will generate the randomized sequence and allocate the individuals to the randomized groups. The participants and the Principal Investigator (EM) will be blinded to the allocation sequence until informed written consent for study participation is obtained. The outcome assessors, data entry personnel and statisticians who analyse the data will be blinded throughout the study as they are not part of the team that delivers intervention or manage the project.

This study uses individual randomization in order to avoid the methodological challenges of cluster randomization, including the clustering effect on statistical power and selection bias, possibility of imbalanced study groups, and the dilution effect
^
23
^. Trial conduct solutions will be put in place to address potential contamination, if any, between the study groups with individual randomization. This include using different staff for each group, education of the participants against contamination
^
23
^, and getting signed nondisclosure agreement from the intervention participants regarding the type of intervention being received. Furthermore, analytical methods that adjust for contamination will also be used. We will also quantify the contamination using a treatment fidelity framework based on the criteria advocated by the Behaviour Change Consortium
^
24
^ and NICE guidance on behaviour change
^
25
^.

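### The mixed models for continuous secondary outcomes let the arms differ at baseline, giving up precision that a common-baseline or baseline-adjusted model would recover

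*Protocol article*

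**What the plan says.** The Data analysis section of the protocol article states the model for continuous secondary outcomes in some detail. It is a linear mixed model in which the baseline, 12-month and 24-month values all enter as responses. The fixed effects are "Study group (intervention vs. control), timepoint (follow-up vs. baseline) and a study group-by-time point interaction", with random effects for ward and participant. Neither a common baseline mean nor a baseline covariate is mentioned.

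For the primary outcome the same section names GEE with "a binomial family with 'log' link function to estimate the relative risk" and sandwich standard errors. It lists no covariates; adjustment is neither planned nor ruled out.

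Two other sections bear on the point. Under Study participants, women enter if "diagnosed with i-IFG (fasting plasma glucose [FPG] 5.6-6.9 mmol/l" (with a 2-hour limit as well), while under Outcomes success requires fasting glucose below 5.6 mmol/l at 24 months. Under Sample size and randomization, individuals are allocated 1:1, and the size is based on two crude proportions: "regression to normoglycemia at two years would be 18% in the control group" and "there would be a 50% relative risk in conversion to normoglycemia with the intervention".

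**The concern.** Individual randomisation makes the arms equal in expectation at baseline. A model with a group main effect ignores this and estimates a baseline difference whose true value is known to be zero. The treatment effect is then the follow-up difference minus the whole observed baseline difference. Since a baseline difference carries over to follow-up only in part, subtracting all of it adds noise.

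What is at stake is the width of the confidence intervals for every continuous secondary outcome analysed this way: fasting and 2-hour glucose, weight, waist, blood pressure, body composition and the psychosocial scores. For the primary outcome, distance from the 5.6 mmol/l cut-off at entry is plausibly prognostic, so adjusting for it could also help, though by less.

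**Working it through.** **1. The plan's own figure.** Inputs from Sample size and randomization: 18% in controls, the effect read as a relative risk of 1.5 (27%), two-sided 5%, "a contamination rate of 15%, and a 10% loss to follow-up".

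- Uncorrected n per arm at 80% power: [1.960·√(2·0.225·0.775) + 0.842·√(0.18·0.82 + 0.27·0.73)]² / 0.09² = 337.
- With the continuity correction: 359. At 90% power: 473.
- Inflated: 359/(0.85·0.90) = 469 and 473/(0.85·0.90) = 618. With 0.75 as divisor: 479 and 631.

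The stated 475 and 625 are reproduced to within about 1.3%. (A relative risk of 0.5 would give 323, so that reading does not fit.) The calculation takes no credit for baseline adjustment and does not concern the secondary outcomes.

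**2. Secondary models, 24-month effect.** Assumptions: n complete cases per arm, equal variance σ² at each visit, and one correlation rho between any two visits (as random intercepts imply).

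- Planned model: Var = (2/n)·2σ²(1−rho) = 4σ²(1−rho)/n.
- Common baseline mean, or baseline as covariate: Var = 2σ²(1−rho²)/n.
- Ratio: (1−rho²)/[2(1−rho)] = (1+rho)/2.

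The article gives no rho, so the values below are assumptions.

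| rho | planned, n·Var/σ² | constrained | ratio | SE smaller by | women needed by planned model |
|---|---|---|---|---|---|
| 0.4 | 2.40 | 1.68 | 0.70 | 16% | 1/0.70 = 1.43 times |
| 0.5 | 2.00 | 1.50 | 0.75 | 13% | 1.33 times |
| 0.7 | 1.20 | 1.02 | 0.85 | 8% | 1.18 times |

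Generalised least squares with three visits gave the same variances at rho 0.5 and 0.7.

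If the timepoint coding means that both follow-ups are pooled against baseline, the ratio is (1+2rho)/3: 0.60, 0.67 and 0.80, with standard errors about 22%, 18% and 11% smaller.

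**3. Unequal variances.** The entry limits compress the baseline spread of fasting and 2-hour glucose. If k is the baseline SD divided by the follow-up SD, the ratio becomes (1−rho²)/(1+k²−2·k·rho). The denominator exceeds the numerator by (k−rho)², so adjustment is never worse, but the gain can shrink. With k = 0.7 and rho = 0.5, both assumed, it is 0.75/0.79 = 0.95 instead of 0.75.

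**4. Primary model.** Simulation of 1,500 trials per scenario at 18% vs 27%, with 427 women per arm (475·0.90) and contamination ignored. Modified Poisson regression with robust standard errors was fitted with and without a standardised, normally distributed baseline covariate. The article does not give the covariate's strength, so it is assumed.

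| odds ratio per SD | variance ratio, log RR | power, crude → adjusted |
|---|---|---|
| 1.5 | 0.97 | 0.88 → 0.89 |
| 2 | 0.95 | 0.88 → 0.89 |
| 3 | 0.86 | 0.88 → 0.92 |

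The mean relative risk stayed near 1.5 in both analyses. A second simulation, with baseline glucose truncated to the entry range, 855 women and standardisation from a logistic model, gave variance ratios of 0.97 to 0.89 for an assumed AUC of 0.61 to 0.74.

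**The case against.** The planned mixed model is a standard, unbiased repeated-measures analysis that uses all available data. It contradicts nothing in the article, concerns secondary outcomes only, and no sample size rests on it. All of that stands, and it limits the point to efficiency. But the fixed effects are written out, so this is a stated choice and not a detail left to an analysis plan. The more precise model needs no new data.

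Three stronger readings are tempting, and the article supports none of them.

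- **That the primary relative risk is unadjusted.** The section names the family, link and standard errors and is silent on covariates. An analysis plan that is not shown may add them. All one can say is that no adjustment is stated.
- **That chance imbalance in baseline glucose biases the result.** Under randomisation, such imbalance is part of the sampling variation that the standard error already covers. Neither bias nor type I error is affected.
- **That the trial is short of power and needs the adjustment to make up for it.** The stated sizes are reproduced, and simulated crude power with 10% loss is about 0.88. How the 15% contamination should enter is a separate question, which this check does not settle.

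It is also fair to object that log-binomial non-convergence arises only once a continuous covariate is added. For that reason, a recommendation to adjust should name the fitting method.

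**Conclusion.** The point holds for the continuous secondary outcomes. As written, the model estimates a difference in change and gives up 15–30% of the variance for assumed baseline-to-follow-up correlations of 0.7 to 0.4, or about 8–16% of the standard error. This rests on complete data, compound symmetry and an assumed rho. The gain is likely to be smaller for fasting and 2-hour glucose, whose baseline spread is restricted by the entry criteria.

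For the primary outcome the point is only a modest supporting improvement: roughly 3–14% less variance of the log relative risk, and about one percentage point of power if baseline glucose is a moderate predictor. The planned analyses remain valid throughout.

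**What to change.** - **Secondary models.** Drop the group main effect so that the arms share one baseline mean, with group-by-time terms at 12 and 24 months. All participants and visits stay in the model. Alternatively, use the baseline value as a covariate with the follow-up values as responses. For fasting and 2-hour glucose, allow the variance to differ between visits. Report the planned model as a sensitivity analysis. State whether 12 and 24 months are separate levels or pooled.
- **Primary model (optional, smaller gain).** Prespecify continuous baseline fasting glucose as a covariate. Fit a modified Poisson GEE with log link and the sandwich standard errors already planned, or standardise from a logistic model to keep a marginal relative risk. Either avoids the convergence failures to which a log-binomial fit with a continuous covariate is prone. Report the unadjusted relative risk alongside.

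The cost is a few lines of analysis-plan wording. The baseline measurements are already scheduled, and the Trial status section places the trial in screening, so the change can be fixed before any follow-up data exist.

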### Ethics approval

The study was approved by the Institutional Human Ethics Committee of the Central University of Kerala (CUK/IHEC/2019/034_A, 21
^st^ November 2019). Written informed consent will be obtained from all study participants. The risk from the intervention to the participants is anticipated to be negligible as the intervention involves only lifestyle modification and no pharmacological drugs. Data safety monitoring will be done by the research team.

## Discussion

This paper describes the protocol for an intense lifestyle intervention program among women with i-IFG to facilitate regression to normoglycemia at 24 months. This study will provide the first evidence on the effects of lifestyle intervention in regressing i-IFG to normoglycemia among Indians. The findings of the study will be disseminated through public engagement, reports and publications.

### Strengths and limitations

This is one of the first studies globally to evaluate the effects of a novel lifestyle intervention among women with i-IFG. Further, the community-based nature of the intervention would facilitate future sustainability and scalability in India and other similar settings. However, since the study population comprises only women, the findings cannot be generalized to men.

### Trial status

The trial is currently in the screening phase.

## Data availability

### Underlying data

No underlying data are associated with this article.

### Extended data

OSF: Randomized Controlled Trial on lifestyle modification intervention for women with isolated impaired fasting glucose.
https://doi.org/10.17605/OSF.IO/8K9XJ
^
37
^.

This project contains the following extended data:

Participant information sheet (screening).pdfInformed consent form screening.pdfScreening tool.pdfParticipant information sheet for the trial (English version).pdfInformed consent form for trial.pdfBaseline assessment.pdf12
^th^ month assessment.pdf24
^th^ month assessment.pdfProcess evaluation tools- participants.pdfProcess evaluation tools - peer mentor.pdfHealth Information leaflet Control.pdf (for control participants)

Data are available under the terms of the
Creative Commons Attribution 4.0 International license (CC-BY 4.0).
